### Eligibility criteria

A veteran is eligible for this trial if he or she 1) receives primary care at the Bronx VA Medical Center or Indianapolis VA Medical Center; 2) is 65 years or older; 3) agrees to consent to HIE between the VHA and non-VHA providers; and 4) has utilized any non-VHA services (including nursing, lab, physician, pharmacy, and/or hospital services) within the previous two years according to records in external HIE network or self-report.

A veteran is excluded if he or she receive services from the Geriatric Resources for Assessment and Care of Elders (GRACE) Team Care [13, 14], a care management model previously implemented within the geriatric service at the Indianapolis VA Medical Center [15], since this program is very similar to the study’s care transitions intervention. If a veteran becomes enrolled in GRACE after enrollment in this trial, he or she will be withdrawn from this trial and notified by mail of the conflict.

### Interventions

This study involves two distinct interventions: 1) an HIE-based event notification message transmitted to the patient’s primary care team when a veteran has a non-VHA acute care encounter; and 2) a care transitions intervention, in which a geriatric care coordinator facilitates follow-up care with a veteran for 30 days following discharge from the acute, non-VHA care facility. These interventions are depicted in Fig. 2.

**Fig. 2 Fig2:**
[figure not shown]
Information flow when a patient has a non-VA acute care encounter. Event notifications are sent via the regional HIE network to the VA for patients in all arms. A coordinator at the VA enters the notification as a note into the EHR for the primary care team to review and co-sign for patients enrolled in arms 1 and 2. For patients in arm 2, a care transition intervention is activated for 30 days post-discharge. VA = Veterans Administration; HIE = Health information exchange; HL7 = Health Level 7; EHR = Electronic health record

The first intervention, event notification, is provided to patients in study arms 1 and 2. Upon utilization of non-VHA acute care, such as an inpatient admission or emergency department (ED) visit, an HL7 admission-discharge-transfer (ADT) message is electronically sent from the acute care facility to an HIE network connected to the two participating VHA sites. In New York, this is the Bronx RHIO. In Indianapolis, this is the Indiana Health Information Exchange. Descriptions of these networks is provided at the end of this section. Each HIE network responds to the ADT message by notifying (or alerting) the VHA that an enrolled patient has visited a non-VHA care facility.

The ADT alert triggers the event notification intervention. Following notification of the non-VHA acute care event, study coordinators at the two VHA sites send an internal electronic note within the VHA’s EHR system to the veteran’s primary care medical home team (referred to within the VHA as a PACT team). This note, which becomes part of the veteran’s medical record, identifies the non-VHA care facility and provides information on the reason for the visit or chief complaint. It further provides details on the external provider and how to contact them. An example message is depicted in Fig. 3.

**Fig. 3 Fig3:**
[figure not shown]
Screenshot of a non-VA encounter note entered into the VA EHR for a patient in either study arm 1 or arm 2. The note must be acknowledged by a member of the patient’s primary care team

The second intervention, a standardized care transitions intervention facilitated by a geriatric care coordinator, is provided to study patients in arm 2 only. In addition to alerting the PACT team, study coordinators at the two sites provide an electronic notification of the non-VHA acute care event to a geriatric care coordinator. While the background of the care coordinator can vary, both sites used geriatric social workers to fill this role. The care coordinators review the veteran’s medical record in the EHR, and they contact the veteran to schedule an in-home visit within 1–5 days following discharge from the external hospital or ED. If a patient is discharged to a rehabilitation setting, the home visit should occur within 1–5 days after rehabilitation facility discharge.

After the home visit, care coordinators perform at least 3 follow-up phone calls for ongoing education and counseling over the subsequent 30 days. The home visit and any subsequent phone calls are documented in clinical notes within the VA EHR system.

The care transitions intervention follows a standardized model developed by Coleman [16, 17] and focuses on activation of the patient to manage his or her own care. The model consists of four pillars for transition care, including 1) understanding and self-management of VHA and non-VHA medications; 2) diagnosis-specific education and counseling, and understanding “red flag” symptoms that require medical attention; 3) creation of a patient-centered record containing contact information, conditions, medications, and advance directives; and 4) self-management of follow-up care within the VHA and non-VHA systems. Care coordinators consider themselves coaches to facilitate veteran’s active, independent self-management of health rather than passive recipients of service. They prefer that veterans schedule follow-up appointments, resolve medication problems, initiate behavioral changes, and complete rehabilitation exercises themselves. Yet the coordinators emphasize they are available for help and encouragement during the 30-day period.

The Bronx Regional Health Information Organization (Bronx RHIO) is a HIE that includes hospitals, physician offices, and long-term care organizations, among others. These providers collectively deliver a majority of the care received by the 1.4 million residents of the Bronx, including over 95% of the borough’s annual hospital discharges, more than 600,000 annual emergency care visits, and 4.5 million annual ambulatory care visits. The Bronx RHIO facilitates secure, interoperable HIE within the borough and connects its jurisdiction to the rest of the state via the Statewide Health Information Network for New York. The providers at the Bronx VA Medical Center have had access to the Bronx RHIO since 2008.

The Indiana Health Information Exchange (IHIE) is a non-profit organization that facilitates health data exchange, including governance as well as security, across an information technology network that connects over 140 hospitals, long-term care facilities, rehabilitation centers, community health clinics and other healthcare providers in Indiana. This network serves more than ten million patients and over 30,000 physicians throughout the country. On top of the network, IHIE offers a variety of patient and population information services such as clinical messaging, analytics, and ADT alerts. IHIE has exchanged data with the VHA since 2011 when it began sending summary of care documents for veterans enrolled in the Veterans Lifetime Electronic Record program [18].

### Outcomes

The primary outcome measure is VHA and non-VHA hospital admission or readmission 90 days after non-VHA hospital or ED discharge (or, if the patient is not discharged home, 90 days after discharge home from a rehabilitation facility). Data on VHA and non-VHA hospital use will be retrieved through the regional HIE partner, the EHR system, and the corporate VHA data warehouse. We chose hospital admission or readmission as the primary outcome because this measure is 1) the most commonly reported outcome in studies of geriatric care transitions interventions [16, 19–22] and a common outcome reported in studies of HIE [23, 24], enabling comparison of study findings with others; 2) frequent; 3) important to patients, providers, and policymakers; and 4) can be ascertained objectively with low risk of bias.

Secondary outcome measures were selected to provide information on intermediate outcomes addressed by the HIE and care transitions intervention components. They include:Post-acute care follow up. Timely VHA follow-up will be defined as a follow-up visit with any VHA provider within 30 days of non-VHA hospital discharge or ED visit. Timely phone call will be defined as VHA PACT phone call within 7 days of non-VHA hospital discharge or ED visit. We will obtain VHA encounter and phone call dates from the EHR system, and non-VHA encounter dates will be obtained from the HIE networks.High-risk medication discrepancies, defined as the number of discrepancies in medications classified as high risk for hospitalized older adults, including opioid analgesics, insulin, non-steroidal anti-inflammatory drugs, digoxin, antipsychotics, sedatives/hypnotics, and anticoagulants [25–27]. We will obtain a count of high-risk discrepancies based on medical record review and patient or caregiver interview 30 days after non-VA hospital discharge.Care Transitions Measure. This measure of condition self-knowledge and transitional care quality from the patient’s perspective is ascertained by patient or caregiver interview 30 days after non-VHA hospital discharge. A 3-item questionnaire, previously developed and validated [28], will be used. The questionnaire includes items such as “After I left the hospital, I had all the information I needed to be able to take care of myself” with the response options strongly agree, agree, disagree, strongly disagree, and don’t know.Process measures, which provide information on processes influenced by HIE-notifications and by care transitions intervention components. We will calculate frequency of HIE-access by providers (login percent per encounter; login duration; tabs browsed) through system audits provided by Bronx RHIO and Indiana HIE. We will calculate frequency of veteran contacts (in person and telephone) by PACT team and care transitions coordinator, using EHR chart review and coordinator logs. We will calculate the percentage of care transitions intervention components delivered that were indicated using coordinator logs.

Qualitative outcomes will include the following:Perceptions of providers as well as veterans on the event notification alerts sent following an acute care event. Do patients perceive these alerts as valuable? Do providers view the alerts as helpful or a hindrance to the care they provide? How can the alerts be delivered in a manner that better supports workflow and patient reengagement following an acute care event?Why do veterans seek acute care outside of the VHA system? While the VHA has enabled greater access to VHA providers, it is not always clear why veterans choose to receive non-VHA services during an acute care event.

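### As worded, the 30-day VHA follow-up outcome does not exclude the arm-2 coordinator's home visit, so delivering the intervention can itself count as the outcome and bias arm-2 contrasts upward.

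*Protocol article*

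**What the plan says.** Arms are numbered here as in the Interventions section: arm 1 is notification only, arm 2 is notification plus care transitions, and arm 3 is the retrospective control.

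- **Outcome (Outcomes section).** "Timely VHA follow-up will be defined as a follow-up visit with any VHA provider within 30 days of non-VHA hospital discharge or ED visit". The source is stated next to it: "We will obtain VHA encounter and phone call dates from the EHR system".
- **Companion phone outcome (same section).** "Timely phone call will be defined as VHA PACT phone call within 7 days of non-VHA hospital discharge or ED visit". This one is limited to the primary care (PACT) team.
- **Process measure (same section).** In-person and telephone contacts by the PACT team and by the coordinator are counted separately, from chart review and coordinator logs.
- **Intervention content (Interventions section).** Coordinators review the record and "they contact the veteran to schedule an in-home visit within 1–5 days following discharge from the external hospital or ED". On recording: "The home visit and any subsequent phone calls are documented in clinical notes within the VA EHR system". On staffing: "While the background of the care coordinator can vary, both sites used geriatric social workers to fill this role". This component "is provided to study patients in arm 2 only". The section opens by saying that "a geriatric care coordinator facilitates follow-up care with a veteran for 30 days following discharge from the acute, non-VHA care facility".
- **Analysis (Statistical methods section).** Secondary outcomes are tested much as the primary is, and the primary model's group term sets arm 2 against notification only or no notification. When this section names the binary follow-up outcome, it calls it scheduled follow-up rather than a completed visit.

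**The concern.** The outcome should show whether patients are seen again within VHA after an outside acute event. Arm 2 has a visit built into its treatment, delivered by VA staff, inside the outcome window and recorded in the outcome's data source. Arms 1 and 3 cannot have that visit. If it counts, part of any arm-2 advantage reflects delivery of the intervention and not additional VHA follow-up. A reader of the results could not tell the two apart, and the bias can only run towards arm 2.

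**Working it through.** The article gives no rate, effect or power for timely follow-up, so there is no planned figure to reproduce. The check traces the definition and then illustrates the size.

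**Tracing the definition**

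1. Who counts: any VHA provider. The term is not defined and nobody is excluded.
2. When: within 30 days of discharge or ED visit. The home visit is planned for days 1 to 5, so it falls inside the window.
3. Data source: VHA encounter dates from the EHR. The home visit is documented in that EHR.
4. Who can have the visit: arm 2 only.
5. Contrast: arm 2 against the others.

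Steps 2, 4 and 5 are explicit. Step 1 (the social worker is a VHA provider) and part of step 3 (the clinical note yields a qualifying encounter) are readings. They are the natural ones, given the word any and the PACT limit placed on the phone outcome but not on this one.

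**Size if the home visit counts**

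Let q be the share with other VHA follow-up within 30 days, taken as equal in all arms (no true effect). Let d be the share of arm-2 patients who get the home visit within 30 days, independently of other follow-up. Both are assumptions.

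- Arm-2 rate as defined: q + (1 − q)d
- Rate in the other arms: q
- Built-in gap: (1 − q)d

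The last two columns give the chance of a two-sided p < 0.05 when there is no true effect on other VHA follow-up. They use the sample-size section's inputs: 7 patients per PACT and an intraclass correlation of 0.05 give a design effect of 1 + 6 × 0.05 = 1.30. For 155 v 311, effective numbers are 155/1.3 = 119 and 311/1.3 = 239. For arm 2 v arm 1 alone, 600 enrolled × 25–30% with an event = 150–180, or 75–90 per arm; 82 per arm is used, before design effect.

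| q | d | Arm 2 v other | Gap (points) | 155 v 311 | 82 v 82 |
|---|---|---|---|---|---|
| 0.3 | 0.25 | 47.5% v 30% | 17.5 | 0.90 | 0.52 |
| 0.3 | 0.75 | 82.5% v 30% | 52.5 | >0.99 | >0.99 |
| 0.5 | 0.25 | 62.5% v 50% | 12.5 | 0.61 | 0.29 |
| 0.5 | 0.75 | 87.5% v 50% | 37.5 | >0.99 | >0.99 |
| 0.7 | 0.25 | 77.5% v 70% | 7.5 | 0.32 | 0.16 |
| 0.7 | 0.75 | 92.5% v 70% | 22.5 | >0.99 | 0.91 |

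If coordinator visits do not count, the gap is 0 and the level is the nominal 0.05.

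**Dependence on independence.** In general the gap is the share of arm-2 patients with a home visit and no other VHA visit. It lies between max(0, d − q) and min(d, 1 − q). At q = 0.7, d = 0.25 that is 0 to 25 points; at q = 0.5, d = 0.75 it is 25 to 50 points. It is never negative, so the direction does not rest on independence, but the size does.

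**The case against.** The strongest case against is that exclusion may have been intended all along.

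- The coordinator is never called a provider. The abstract and the Trial design section mention the coordinator or social worker separately from the providers who are alerted.
- In the Interventions section, coordinators act as coaches who want veterans to book their own follow-up. On that usage, follow-up is what the coaching should produce. The name used in Statistical methods, scheduled follow-up, also fits an appointment better than an intervention visit.
- Coordinator contacts already have their own process measure, so the investigators can identify them and may have meant to keep them apart.
- Which EHR notes count as encounters is an extraction rule that an article may leave to a fuller document.

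These are fair points about intent, and the last would excuse silence. But the article is not silent: it states who counts, in the widest terms, beside an outcome where it chose a narrower rule. If exclusion was intended, the wording does not say so.

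A reader might go further and infer that the comparison is circular, that the outcome mostly measures delivery, or that it is bound to show a large benefit. The documents do not support this. With q = 0.6 and d = 0.5 the rates are 80% v 60%, since 0.6 + 0.4 × 0.5 = 0.80, and 60 of arm 2's 80 points are other follow-up. Visits to any VHA provider over 30 days may be common in this population, and the gap shrinks as q rises. Some home visits will not take place. After a rehabilitation stay the home visit is timed from rehabilitation discharge, so it may fall more than 30 days after hospital discharge.

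**Conclusion.** The point holds as a flaw in the stated definition of one secondary outcome. On its natural reading, the rule lets the arm-2 home visit satisfy the outcome and biases contrasts involving arm 2 upward by (1 − q)d under independence. In the grid above this runs from 7.5 to 52.5 points. Those figures rest on assumed q and d, and on the home visit being counted as a visit with a VHA provider, which the article neither states nor rules out. What does not depend on the assumed rates is the direction: if the visit counts, the bias is towards arm 2 or nil.

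The scope is limited. The notification-only versus control comparison is untouched, because neither group has a coordinator. The primary outcome, 90-day admission or readmission, is untouched, and the phone-call outcome is already protected by its PACT limit. The change should be made before analysis, but it does not threaten the trial's main conclusion.

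**What to change.** - Define timely VHA follow-up as a visit, within the existing 30-day window, with any VHA provider other than the study care transitions coordinator. Excluding the coordinator is safer than restricting the outcome to PACT or clinic providers, which could drop genuine home visits by VHA staff outside the study.
- Apply the same encounter rule in all three arms.
- Keep coordinator contacts as the separate process measure already listed.
- Reconcile the two descriptions of the outcome: Outcomes defines a visit, while Statistical methods names scheduled follow-up. State whether a completed visit or a booked appointment is counted.

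The cost is one line in the outcome definition, one wording change in Statistical methods and a filter on the encounter extract, with coordinator logs available to identify the visits to remove. It changes no patient care and needs no new data.

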### Participant timeline

The enrollment and participant timeline is depicted in Fig. 4. Veterans who actively enroll in the study during Phase 1 are placed into one of two arms based on their primary care provider’s PACT team per the cluster design. Non-VHA acute care visits are monitored for both arms using a public health surveillance approach. If a non-VHA visit is detected, the response is driven by the arm into which his or her PACT team was randomized. Regardless of arm, a research team member will contact the veteran 30 days after discharge from the non-VHA facility to conduct an interview over the phone. In the case where a patient is discharged to a rehabilitation or nursing facility, follow-up will occur 30 days after discharge from that facility. A medical chart review is conducted for the 90-day period following discharge to ascertain readmission to a hospital or emergency room visit as well as other secondary outcomes.

**Fig. 4 Fig4:**
[figure not shown]
Overview of patient screening, enrollment, and activation procedures performed by research staff. The figure distinguishes between study arm 1 (notification only) and arm 2 (notification plus care transitions intervention)

### Sample size

Our sample size estimate is based on the primary outcome. Reports of randomized studies of geriatric care transitions interventions have reported 25–45% reductions in hospital readmissions [17, 20, 29]. Based on prior work as well as pilot data gathered within the VHA (unpublished), we postulate that the notification-only group as well as the usual care group will have a 40% readmission rate while the notification-plus-coordination group will have a 26% readmission rate in the 90-day post-discharge period (i.e., a clinically significant 35% reduction).

There are several features of the study that support this large potential effect. First, the targeted patients are at high risk of readmission because they are older veterans who utilize both VHA and non-VHA services, who have been shown in previous studies to have significantly higher readmission rates after acute illness. Second, in contrast to veterans hospitalized in the VHA who routinely receive PACT post-discharge telephone calls and follow-up, this group is naïve to any coordination intervention because PACT teams normally do not respond to non-VHA hospital encounters because they do not know about them. Thus, we postulate more than an incremental effect.

To account for possible dependence of the outcome among patients cared for by the same PACTs (clustering), we estimated the design effect [30] based on an average number of subjects per PACT = 7. Assuming the intraclass correlation is 0.05 (based on pilot data and prior literature [31]), we need to observe a total of 466 patients with non-VHA hospitalizations or ED visits (155 in the notification-plus-coordination group and 311 combined in the notification-only and usual care groups) to detect an effect size of 0.35 with 80% power and a two-tailed test at 5% significance. If the intraclass correlation is smaller (e.g., 0.04), which may be the case for a group of patients whose care is fragmented and perhaps less influenced by primary care team clustering, then the power will be higher.

In order to achieve the target sample size, we will enroll 300 patients at each site, with an estimated 25–30% of enrolled veterans experiencing non-VHA hospital encounters. We anticipate 10–15% attrition due to death or loss to follow up given the average age of veterans in the target population.

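### The sample size of 466 does not follow from the stated intraclass correlation of 0.05: those inputs need at least 488, and 466 gives 75–78% power

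*Protocol article*

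**What the plan says.** All the inputs stand in the Sample size section of the protocol article.

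- Control rate: the "notification-only group as well as the usual care group will have a 40% readmission rate".
- Intervention rate: "the notification-plus-coordination group will have a 26% readmission rate in the 90-day post-discharge period".
- Clustering: "we estimated the design effect [30] based on an average number of subjects per PACT = 7".
- Result: "Assuming the intraclass correlation is 0.05 (based on pilot data and prior literature [31]), we need to observe a total of 466 patients", split as "155 in the notification-plus-coordination group and 311 combined in the notification-only and usual care groups".
- Operating characteristics: "to detect an effect size of 0.35 with 80% power and a two-tailed test at 5% significance". The section describes this 0.35 as a 35% relative reduction (0.14/0.40).

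A sensitivity sentence follows. It begins "If the intraclass correlation is smaller (e.g., 0.04" and concludes that power would then be higher. The section does not name the formula for comparing the two proportions.

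**The concern.** The inputs and the result are all printed, so the calculation can be repeated, and it does not return 466 at an intraclass correlation (ICC) of 0.05. The value that returns 466 is the one the next sentence presents as optimistic.

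Two things are at stake. First, the power claim for the primary outcome is below 80% on the plan's own assumptions. Second, the sensitivity sentence turns what looks like the break-even ICC into a safety margin. The target has practical weight: the Discussion makes larger enrolment or a longer study depend on whether enough non-VHA encounters occur, and 466 is the only target given.

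**Working it through.** **Inputs (protocol article, Sample size).** p1 = 0.26; p2 = 0.40; difference 0.14; allocation 155:311, about 1:2; two-sided 5% (z = 1.96); 80% power (z = 0.8416); 7 patients per PACT; ICC 0.05, with 0.04 as the alternative.

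**Step 1: need without clustering (unpooled variance, k = 2 controls per coordination patient).**

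n1 = (1.96 + 0.8416)² × [p1(1 − p1) + p2(1 − p2)/k] / 0.14²

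= 7.849 × [0.1924 + 0.2400/2] / 0.0196 = 7.849 × 0.3124 / 0.0196 = 125.1

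Total = 3 × 125.1 = 375.3.

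**Step 2: design effect, 1 + (7 − 1) × ICC.** This is 1.24 at ICC 0.04 and 1.30 at ICC 0.05.

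**Step 3: reproduce the printed figure.** At ICC 0.04, 375.3 × 1.24 = 465.4 (155.1 + 310.3). Rounding the total up to 466 and splitting it 1:2 gives 155.3 and 310.7, which print as 155 and 311. Solving backwards, 466/375.3 = 1.2417, so ICC = 0.2417/6 = 0.0403.

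**Step 4: apply the stated ICC.** At ICC 0.05, 375.3 × 1.30 = 487.9, so 488 (162.6 + 325.3, or 163 + 325).

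**Step 5: other formulas.** The formula is not named, so I checked whether another one gives 466 at ICC 0.05, 7 per PACT, 1:2 and two-sided 5%.

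| Formula | Total at ICC 0.05 |
|---|---|
| Unpooled variance | 488 |
| Arcsine | 513 |
| Pooled variance (Fleiss) | 521 |
| Pooled variance only | 535 |
| Logit Wald | 543 |
| Fleiss with continuity correction | 562 |
| Log relative risk | 593 |

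None does, and 488 is the smallest. Reading 0.35 as a standardised difference gives 375, which does not match either and contradicts the section's own description of 0.35 as a relative reduction.

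**Step 6: power with 155 + 311.** Effective sizes are n divided by the design effect.

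- ICC 0.05, unpooled: 155/1.30 = 119.2 and 311/1.30 = 239.2. SE = √(0.1924/119.2 + 0.24/239.2) = 0.0512. z = 0.14/0.0512 − 1.96 = 0.777; power 78.1%.
- ICC 0.04, unpooled: 155/1.24 = 125.0 and 311/1.24 = 250.8. SE = 0.0500; z = 0.842; power 80.0%.
- Pooled (Fleiss): 75.3% at ICC 0.05 and 77.3% at ICC 0.04.

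**Step 7: could one other input be misprinted instead?**

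- Six patients per PACT gives 375.3 × 1.25 = 469, but the section states "average number of subjects per PACT = 7". The Allocation section supports 7: 25 + 41 = 66 PACTs, and 466/66 = 7.06.
- A 1:1 design with pooled variance needs 175.9 per group, or 2 × 175.9 × 1.30 = 457. That contradicts the printed split.
- A one-sided test with continuity correction and 8 per PACT gives 467. That contradicts both the two-tailed test and the 7.

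**The case against.** Four points can be made for the text as printed.

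1. **The ICC 0.04 origin is an inference.** It holds only for the unpooled formula. With pooled variance, ICC 0.04 needs about 497, and 466 corresponds to an ICC of about 0.027; with arcsine, to about 0.03. This stands: 0.04 is the likely source, not a proven one. It does not rescue the figure, because no two-proportion formula gives 466 at ICC 0.05.

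2. **The sensitivity sentence is literally true.** It says only that power rises as the ICC falls, and it does, from 78.1% to 80.0% unpooled or from 75.3% to 77.3% pooled. This stands as a matter of wording. But the sentence directly follows a claim of 80%, so a reader will take it to mean more than 80%, and neither formula supports that.

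3. **The gap is small and rounding covers most of it.** An average of 6.5 per PACT and an ICC of 0.045 would print as 7 and 0.05. They give 375.3 × (1 + 5.5 × 0.045) = 468. This is fair on size, but it needs both inputs at the edge of their rounding and still does not reach 466.

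4. **True power may not be below 80%.** The plan applies 7 per PACT to both groups. If half the 66 PACTs hold the 155 coordination patients, that is 155/33 = 4.7 per PACT. If controls come from all 66 (an assumption), they also average 311/66 = 4.7. The design effect is then 1 + 3.7 × 0.05 = 1.185, the need 375.3 × 1.185 = 445, and power at 466 about 82%. If instead all controls came from the other 33 PACTs, they would average 311/33 = 9.4, with a design effect of 1.42 and power of about 79%. So the finding is that the printed result does not follow from the printed inputs. What power the trial will achieve is a separate question, and the cluster sizes stated do not settle it.

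**Conclusion.** The sample size statement is wrong as written. On the plan's own inputs, 80% power needs at least 488 patients, 22 more than stated (22/466 = 4.7%). With 466, power at ICC 0.05 is 78.1% under the unpooled formula, a loss of 1.9 points, or 75.3% under the pooled formula, a loss of 4.7 points. Under the one formula found that reproduces both the total and the split at an ICC the section names, ICC 0.04 is the value that gives 80%, so it offers no reserve.

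This rests on the plan's single design effect of 1 + 6 × ICC for both groups, a 1:2 comparison of 26% with 40%, and a two-sided 5% test. The mismatch does not depend on the choice among the two-proportion formulas tried; only the attribution to 0.04 does. The error is modest and leaves the design and analysis untouched, but it affects the figure on which the power claim and any decision to extend recruitment rest.

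**What to change.** In the Sample size section of the protocol article, name the two-proportion formula, then choose one of two corrections:

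- keep ICC 0.05 and state 488 patients (163 + 325) if the formula is unpooled, or 521 (174 + 347) if it is pooled; or
- keep 466 (155 + 311) and state its power: about 78% at ICC 0.05 and 80% at ICC 0.04 if unpooled, or 75% and 77% if pooled.

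In either case, rewrite the sentence on 0.04 so that it gives the recomputed power at that value. With 466 it must not suggest power above 80%.

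The second option costs only a text correction and a slightly less favourable stated power. The first also raises the number of patients with encounters to be observed by 22 under the unpooled formula, or by 55 (521 − 466) under the pooled one.
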